### Ethical aspects

This study has received the approval of the Ethics and Clinical Research Committees of the Balearic Islands. Written informed consent of participants will be obtained before group allocation. Patients will have been properly informed about the study characteristics and objectives previous to study inclusion. They will also be informed about the voluntary nature of participation and the possibility to leave anytime with the guarantee that they will still receive treatment as recommended by their GP. Patients allocated to control group will be offered to follow the intervention group recommendations once the study is finished, if final results recommend doing so. Confidentiality of data will be guaranteed.

## Discussion

This study represents a great opportunity for the improvement with minimal costs of the effectiveness of depression treatment. Results of a preliminary study [9,13] pointed out that significant improvement of depressive symptoms can be achieved with this simple intervention. Its feasibility for the sanitary system derives from its low time consumption for health providers and the low cost of its implementation. Moreover, no significant adverse events or security problems derived from this intervention are expected.

Considering the low-restrictive nature of inclusion and exclusion criteria of the present study, problems for the recruitment of patients are not expected. The sample size will enable the determination of the profile of patients that could benefit from this simple intervention. It will also provide a better understanding of the reasons why some patients do not adhere to these recommendations, with the objective of eliminating this trend. The development of this research line in Primary Health Care settings is of great interest as well.

However, this study also has some limitations that will be taken into account. The main limitation derives from the fact that although GPs will be blinded to patient allocation, it is presumed that they will easily be able to identify which group the patient has been assigned to in the follow-up assessments. This is a potential bias as GPs could be induced to change pharmacological treatments based on this knowledge. In order to minimize this effect, we will ask participant GPs to stay as oblivious to patient allocation as possible. In case patient allocation is suspected, they will be asked to maintain a neutral attitude to patient comments regarding the recommendations they have received. Raters will also be blinded to treatment condition but, again, it will be easy for them to suspect patient allocation from the information provided by patients during the assessments. This could obviously introduce involuntary bias. To correct this possible bias, self-applied instruments will be preferred as main outcome variables.

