## Methods

### Hypothesis and objectives

The first hypothesis of the present study is that patients assigned to the intervention group receiving specific hygienic-dietary recommendations will show a significantly greater improvement in clinical measures of depression in comparison to control group patients. The second hypothesis is that significant differences in health costs will be found between both groups, with patients in the intervention group showing lower expenses. Therefore, the main objective is to evaluate the effectiveness and efficiency of giving specific hygienic-dietary recommendations to depressive patients in Primary Care settings. Secondary objectives are to evaluate changes in direct and indirect costs, to specify a profile of patients who benefit from this intervention and to identify the most frequent inconveniences for patients leading to non-adherence to these recommendations.

The present study is a randomized controlled clinical trial under “real world” conditions. Patients will be allocated to one of these two conditions:

1 Treatment as usual prescribed by their GP plus specified hygienic-dietary recommendations (intervention group)

2 Treatment as usual prescribed by GP plus unspecified hygienic-dietary recommendations (control group)

The study design is shown in Table 1.

**Table 1 T1:** STUDY SCHEDULE

	***“TRIAGE”***	***BASELINE***	***SIXTH MONTH***	***TWELFTH MONTH***
**Criteria compliance evaluation**	**X**			
**Discussion of the study information leaflet**	**X**			
**Signed Consent Form**	**X**			
**MINI Interview**		**X**		
**Sociodemographic questionnaire**		**X**		
**Clinic questionnaire**		**X**	**X**	**X**

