### Sample size and randomization

Statistical analysis will be based on head-to-head comparisons between the group receiving the hygienic-dietary recommendations and the “treatment as usual” group. Based on previous research, we expect that the mean difference between both groups in the main variable (BDI Total score) will be of at least 3 points (SD=6). Assuming an alpha risk of 0.01 and two tails, with a study power of 90% the corresponding sample size is 119 patients per group. With an estimated withdrawal rate of 20%, the sample size will require approximately 150 patients in each group. Thus, the total sample size of the study will be 300 patients.

Randomization will take place for each patient once participation is agreed to and the written informed consent signed. Every GP participating in this study will be provided with identically sealed envelopes codified with a numerical code that identifies the contents. These codes will be kept by the head of the research team. Half of the envelopes will contain the specific hygienic-dietary recommendations under consideration while the other half will contain “control” unspecified hygienic-dietary recommendations. In all cases, these recommendations will be written on a sheet of paper. The GP will randomly choose an envelope and ask the patient to follow the recommendations written inside.

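### The stated ability of the sample size to identify which patients benefit is not supported: the trial is sized for the overall effect only, and only very strong effect modifiers would be reliably detectable.

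*Protocol article*

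**What the plan says.** Under Hypothesis and objectives, the protocol article lists among its secondary objectives "to specify a profile of patients who benefit from this intervention". The Discussion then says of that aim: "The sample size will enable the determination of the profile of patients that could benefit from this simple intervention". Neither place calls the profile work exploratory. The limitations paragraph of the Discussion deals with blinding and does not return to the matter.

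The only calculation is in Sample size and randomization. It concerns the comparison of the two arms on BDI total score, with a difference of 3 points, SD 6 and two-sided alpha 0.01: "with a study power of 90% the corresponding sample size is 119 patients per group". After allowance for 20% withdrawal, "the sample size will require approximately 150 patients in each group", giving 300 in total. The article gives no interaction size, subgroup size or power for the profile objective.

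**The concern.** A profile of patients who benefit from the advice differs from a profile of patients who improve. The first requires the treatment effect in one kind of patient to be compared with the effect in another, which is a treatment-by-characteristic interaction. A sample chosen to estimate the average effect estimates an interaction much less precisely, so adequacy for the first does not carry over to the second.

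What is at stake is how the profile results will be read. A reader could cite the published protocol as evidence that this analysis was adequately sized. A null interaction might then be taken to show that everyone benefits equally, and a chance positive might be taken as a planned and powered result. Either reading could influence which primary-care patients are given the advice.

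**Working it through.** **Inputs from Sample size and randomization:** difference 3 BDI points; SD 6; two-sided alpha 0.01 (z = 2.576); power 90% (z = 1.282); 119 evaluable per arm; 20% withdrawal; 150 recruited per arm.

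**Assumptions not in the document:** one binary baseline modifier; the same SD of 6 within each subgroup; the same subgroup split in both arms; no baseline adjustment unless stated. Alpha 0.05 is shown beside 0.01 because the article does not say which level applies to this objective.

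**Step 1. The plan's own figure.** n per arm = 2 × SD² × (2.576 + 1.282)² / 3² = 119.04 before rounding. Power at 119 per arm is 0.8999. Inflation: 119 / (1 − 0.20) = 148.75, so about 150. The stated 119, 150 and 300 reproduce. Evaluable patients number 238 (2 × 119) to 240 (300 × 0.80).

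**Step 2. Standard errors at 119 per arm.**
- Overall effect: 6 × √(2/119) = 0.778.
- Interaction: SD × √(2/n₁ + 2/n₂), where n₁ and n₂ are the per-arm numbers in each subgroup.
- 50:50 split (59.5 and 59.5): 1.556, twice the overall value.
- 20:80 split (23.8 and 95.2): 1.945.

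**Step 3. Power for a 3-point interaction**, as Φ(3/SE − z). With an even split and an average effect of 3, this means 4.5 points in one half and 1.5 in the other.

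| Scenario | SE | Alpha 0.01 | Alpha 0.05 |
|---|---|---|---|
| 238 evaluable, 50:50 | 1.556 | 26% | 49% |
| 238 evaluable, 30:70 | 1.697 | 21% | 42% |
| 238 evaluable, 20:80 | 1.945 | 15% | 34% |
| 300 analysed (no withdrawals), 50:50 | 1.386 | 34% | 58% |
| 238, 50:50, baseline-adjusted, assumed correlation 0.5 | 1.556 × √0.75 = 1.347 | 36% | 60% |

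**Step 4. Interaction detectable with 90% power at alpha 0.01**, as (2.576 + 1.282) × SE:
- 50:50 split: 3.858 × 1.556 = 6.0 points, twice the planned overall effect.
- 20:80 split: 3.858 × 1.945 = 7.5 points.

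At alpha 0.05, the 50:50 figure is (1.960 + 1.282) × 1.556 = 5.0 points.

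**Step 5. Size needed for a 3-point interaction.** With an even split, N = 16 × 36 × (2.576 + 1.282)² / 9, or about 953 evaluable patients for 90% power at alpha 0.01. At alpha 0.05 it is about 673.

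These figures are for one modifier. Testing several with multiplicity control would lower power further.

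**The case against.** The strongest reply is that a 3-point interaction is the wrong benchmark. It describes two halves that both benefit, by different amounts. If the question is who benefits and who does not, the simplest case is one half gaining 6 points and the other none, which still averages 3. The interaction is then 6 points, with power Φ(6/1.556 − 2.576) = 90% at alpha 0.01 and about 97% at 0.05. This stands. A reader might infer that the Discussion sentence is simply false, but the document does not support that: in this scenario the sample has its planned power. The scenario is favourable, however, since it needs a single modifier, an even split and an all-or-nothing effect. If 80% of patients benefit and 20% do not, the same average implies 3/0.8 = 3.75 versus 0, and power is Φ(3.75/1.945 − 2.576) = 26%.

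The second reply is that the power figures depend on assumptions the article does not make. This also stands, and they are offered as illustration. Full follow-up or moderate baseline adjustment raises power, but not to 80% for a 3-point interaction. A stronger correlation would help more: at an assumed 0.7, power is about 55% and 77%. The article gives no correlation.

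Third, a reader might infer that the authors intend a multiply tested subgroup search, an analysis of responders within the intervention arm, or separate subgroup p-values. The Statistical analysis section states none of these. The choice of moderators and model is commonly left to a full protocol or analysis plan not shown here, so its absence is no fault.

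Finally, the sentence is a Discussion remark that governs no enrolment or decision rule. That limits the consequence. But it is an unqualified claim about a declared secondary objective, and an analysis plan could not supply the missing support for it.

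**Conclusion.** The point holds as a claim that the stated design does not support. The sample size is right for the overall 3-point difference, and nothing here affects the primary conclusion. It is not shown to be adequate for identifying who benefits. Under the assumptions listed, and before any multiplicity control, power for a 3-point interaction ranges from about 15% (20:80 split, alpha 0.01) to about 60% (even split, alpha 0.05, with baseline adjustment at an assumed correlation of 0.5). Only an interaction of about 6 points in an even split reaches 90% power at alpha 0.01. The fair description is that the claim is unsupported except for very strong modifiers. It should be corrected because it bears on what the secondary objective can conclude.

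**What to change.** Replace the Discussion sentence with wording such as: *The study is sized for the overall effect only. With about 240 evaluable patients, and for a single evenly split characteristic, only interactions of about 6 BDI points or more would be detected with 90% power at a two-sided alpha of 0.01. The analysis of which patients benefit is exploratory.* State the assumptions behind the 6-point figure (SD 6, no baseline adjustment) beside it. Under Hypothesis and objectives, label the profile objective as exploratory.

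The cost is a less ambitious stated objective. Enrolment, the sample size and the primary analysis do not change.

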## Abbreviations

BDI: Beck Depression Inventory; BMI: Body Max Index; BP: Blood Pressure; CSRI: Client Service Receipt Inventory; GP: General Practitioner; HR: Heart Rate; MINI: Mini International Neuropsychiatric Interview; STAI: State-Trait Anxiety Inventory; EuroQol: European Quality of Life self-report questionnaire.
